#### Qualitative phase.

The interview guide will be refined based on the results of the quantitative phase. Additionally, the findings from the quantitative questionnaires will inform the selection of participants for the interview phase. The interview will take place in the Faculty of Nursing and Physiotherapy of the University of Lleida. Interviews will be conducted in either Spanish or Catalan (participants’ choice) and will be recorded in audio or video, with participants’ previous consent. Once all questionnaire data has been analysed, a subgroup will be created based on the results obtained, which will be related to the categories identified in the PedsQL™ Family Impact Module [15] and the Zarit Burden Interview [16], both in their Spanish versions.

#### Sample size considerations.

The quantitative sample size was estimated using GRANMO (estimation of a population mean). Assuming a 95% confidence level, a standard deviation of 21, based on Spanish normative data for the PedsQL-Family Impact Module [17]. Assuming an accessible finite hospital population of approximately 40 eligible caregivers and a precision of ±5 points on the 0–100 scale; the required sample is n = 26 completers. Allowing for an anticipated 15% attrition rate, the recruitment target is approximately 31 caregivers. This sample ensures estimation of the mean PedsQL-FIM score with adequate precision for the finite population. In addition, with n = 25–30 completers, two-tailed tests at α = 0.05 will have approximately 80% power to detect correlations of r = 0.50–0.54, providing sufficient power for moderate-to-large associations while acknowledging that smaller effects may be underpowered

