### Data analysis

#### Quantitative data.

The quantitative data will be analysed using descriptive statistics and frequency counts. Sociodemographic characteristics will be described. Descriptive statistics will be reported with means and standard deviations for continuous variables with normal distribution (age, child’s age, PSS-14, PedsQL-FIM, ZBI), or medians and interquartile ranges for variables without normal distribution. For categorical variables (sex, educational level, severity), both absolute and relative frequencies will be presented.

For the inferential analyses, Spearman’s correlations will be used to explore relationships among questionnaires (stress, burden, and quality of life) as well as to correlate caregiver outcomes (stress, burden, quality of life) across subgroups defined by sociodemographic variables (e.g., economic status, education level), child-related variables (e.g., severity of Cerebral Palsy, mobility), and caregiving factors (e.g., relation with the child). Primary analyses will use multivariable linear regression to model each caregiver outcome: (i) perceived stress (PSS-14), (ii) caregiver burden (ZBI), and (iii) quality of life (PedsQL-FIM total). Separate regression models are specified for stress, caregiver burden, and quality of life, consistent with their conceptualization as co-primary constructs, each examined to characterize different but interrelated dimensions of caregiver outcomes. Given the finite population constraints (approximately 40 eligible caregivers)), each model will include only the most relevant predictors (up to 2–3 per model), carefully selected on priori literature and clinical plausibility (e.g., socioeconomic status, caregiving duration, and child functional severity/mobility). This parsimonious approach reduces multiple comparisons and allows adjustment for potential confounders. Model assumptions, including linearity, normality of residuals, and homoscedasticity, will be evaluated using standard diagnostics such as residual plots and Shapiro-Wilk tests. If model assumptions are violated, data transformations or alternative statistical techniques will be considered. Results will be reported as standardized regression coefficients (β) with 95% confidence intervals. Analyses will be conducted using IBM SPSS Statistics v28 (or equivalent software) with significance level of α = 0.05 (two-tailed).

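### At the roughly 26 completers the plan expects, power for a correlation of 0.50 is about 70–75%, not 80%; the r = 0.50 end of the power statement should be dropped

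*Protocol article*

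**What the plan says.** Under *Sample size considerations*, the protocol article sizes the quantitative phase on the precision of the mean PedsQL-FIM score and concludes that "the required sample is n = 26 completers". It continues: "Allowing for an anticipated 15% attrition rate, the recruitment target is approximately 31 caregivers". As an addition to that calculation, it states that "with n = 25–30 completers, two-tailed tests at α = 0.05 will have approximately 80% power to detect correlations of r = 0.50–0.54", calls this sufficient for moderate-to-large associations, and concedes that smaller effects may be underpowered. The power sentence does not name the correlation coefficient.

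Under *Data analysis – Quantitative data*, the only correlation method named is Spearman's: "Spearman’s correlations will be used to explore relationships among questionnaires (stress, burden, and quality of life"), and the same method is extended to sociodemographic, child-related and caregiving factors. The primary analyses are multivariable linear regressions. The Discussion describes the whole protocol as exploratory rather than confirmatory.

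**The concern.** The power sentence covers a span of completers that reaches 30, and its more favourable detectable correlation, 0.50, depends on that end. The sentences just before it expect about 26. A reader who takes 0.50 as the correlation this study can detect with 80% power is relying on an enrolment the plan does not expect. The planned test is also Spearman's, which on continuous bivariate normal data has somewhat less power than Pearson's for the same underlying correlation.

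The stake is how a non-significant correlation is read. This is the only power statement in the article. Its caveat about smaller effects implies that 0.50 itself is covered. If power there is 70–74%, the chance of missing such a correlation is 26–30%, not 20%.

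**Working it through.** **Inputs.** From *Sample size considerations*: two-sided α = 0.05; power about 80%; r = 0.50–0.54; 25–30 completers; 26 completers required; about 31 recruited; 15% attrition; SD 21; precision ±5; accessible population about 40. From *Quantitative data*: Spearman's correlation.

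**1. Number of completers.**
- Without finite-population correction: (1.96 × 21 / 5)² = 67.8.
- Corrected for N = 40: 25.2–25.4, depending on the form of the correction, rounded up to 26. This reproduces.
- Recruitment: 26 / 0.85 = 30.6, rounded up to 31. This reproduces.
- Expected completers: 31 × 0.85 = 26.35.

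**2. The printed power, with the ranges read as paired ends.** Fisher z: power = Φ(atanh(r) × √(n − 3) − 1.96).
- n = 25, r = 0.54: Φ(0.604 × 4.690 − 1.96) = Φ(0.874) = 80.9%.
- n = 30, r = 0.50: Φ(0.549 × 5.196 − 1.96) = Φ(0.894) = 81.4%.

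Both agree with about 80%. For a Spearman test, simulation with r taken as the Spearman coefficient gives 80.0% and 80.6% at the same ends. With r as the underlying Pearson correlation it gives about 76–77% at both.

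**3. What r = 0.50 needs.** n = ((1.96 + 0.842) / 0.549)² + 3 = 29.0. Power is 80.0% at n = 29 and 81.4% at n = 30. Thirty completers would mean one loss among 31 (about 3%), or 36 recruits at 15% attrition. If losses are independent at 15% (an assumption), the chance of 29 or more completers from 31 is 14%, and of 30 or more, 4%.

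**4. Power at n = 26.** √(n − 3) = √23 = 4.796.

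| Test and meaning of r | r = 0.50 | r = 0.54 |
|---|---|---|
| Pearson, Fisher z | 75.0% | 82.6% |
| Spearman, simulated, r = underlying Pearson | 70% | 78% |
| Spearman, simulated, r = Spearman coefficient | 74% | 81% |
| Spearman, Fisher z with variance (1 + r²/2)/(n − 3) | 70.0% | 77.2% |
| Spearman, Fisher z with variance 1.06/(n − 3) | 72.5% | 80.4% |

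The simulations used at least 100,000 bivariate normal samples without ties and the t-approximation critical value. Simulated Pearson power at r = 0.50 is about 77%.

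**5. Correlation detectable with 80% power at n = 26.**
- Pearson: tanh((1.96 + 0.842) / 4.796) = tanh(0.584) = 0.526.
- Spearman, simulated: underlying Pearson 0.55 (power 80.1%). The corresponding Spearman coefficient is (6/π) × arcsin(0.55/2) = 0.53.
- The two Spearman variance formulas give 0.557 and 0.538.

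**The case against.** The strongest reply is that nothing is miscalculated. The two ranges read naturally as paired, and both ends give about 80%. The expected 26 completers lie inside 25–30, and a range around an anticipated count is a reasonable sensitivity statement; it extends below the target as well as above it. The article nowhere claims 80% power for the specific combination of r = 0.50 and 26 completers. At 26, the detectable Pearson correlation of 0.526 falls inside the stated range. All of this stands.

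A reader might infer that the figure belongs to a Pearson test and is therefore wrong for the planned Spearman analysis. The article names no coefficient, and the figure also reproduces for Spearman when r is the Spearman coefficient, so that inference is not supported. A reader might also infer that the 25–30 range contradicts the 15% attrition. It does not, since 26 is within it; only its upper end is out of line with the expected number.

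What the reply does not remove is that the range presents 0.50 as detectable with about 80% power, and the plan's own numbers do not deliver that under any of the methods tried.

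**Conclusion.** The point holds in a narrow form. At the number the plan expects, power for r = 0.50 is about 75% for Pearson (Fisher z) and about 70–74% for the planned Spearman test, so 5 to 10 percentage points below the printed figure. The 70–74% range reflects what r is taken to mean, and assumes bivariate normal scores without ties. The upper end of 0.54 is approximately right at 26 completers.

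The consequence is modest. The sample size rests on the precision of the PedsQL-FIM mean, which reproduces; the primary analyses are regressions; and the correlations are exploratory. The article does not say that a null correlation will be taken as evidence of no association.

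It is tempting to go further for ordered factors such as education or severity. With one variable cut into three equal groups, simulated Spearman power at n = 26 and an underlying r of 0.50 is about 63%. The direction is sound, but the article does not give the number or balance of the levels, so that figure illustrates an assumption and is not a property of the plan.

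**What to change.** In *Sample size considerations*, replace the range with the figure for the planned number and test, for example:

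> With 26 completers (31 recruited, 15% attrition), a two-tailed Spearman test at α = 0.05 has approximately 80% power for correlations of about 0.53–0.55, depending on whether r is the Spearman or the underlying Pearson coefficient, and about 70–74% for 0.50; power is lower for factors with few ordered levels.

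This drops 0.50 as a correlation detectable with 80% power and names the coefficient. It changes one sentence, with no change to recruitment or to the planned analyses. The only cost is a slightly less favourable stated figure.

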#### Study status and timeline.

At the time of manuscript submission, the study has not yet started. The start date of the recruitment period for this study is expected to begin 02/06/2025 and expected to be completed by end of June 2025. Data collection is anticipated to be finalized by August 2025, and preliminary results are expected to be available by September 2025. This timeline is subject to minor adjustments depending on recruitment rates and operational logistics S1 Fig (Fig 1.)

**Fig 1 pone.0342763.g001:**
[figure not shown]
Participant timeline: Schedule of enrollment, interventions and assesments. PSS-14: Perceived Stress Scale, PedsQL-FIM: Qualoty of Life by PedsQL^TM^ Family Impact Module, ZBI: Zarit Burden Interview.

### Measures

#### Perceived Stress Scale (PSS-14).

The PSS-14 is short and easy adaptation of the original Perceived Stress Scale (PSS), with the original author being Cohen, S. The European Spanish adaptation was conducted by Remor, E. [18].

The PSS measures the degree to which individuals perceive life situations as stressful over the past month, focusing on subjective control over unpredictable events and the distress associated with perceived lack of control. The PSS is more closely related to subjective evaluations of life events than objective measures of stressors [19]. The 14-item European Spanish version of the Perceived Stress Scale (PSS-14) will be employed to assess caregivers’ levels of perceived stress. This instrument comprises 14 items, each rated on a five-point Likert scale ranging from 0 to 4 (0 = never, 1 = rarely, 2 = sometimes, 3 = usually, 4 = almost always), yielding a total score between 0 and 56. Higher scores indicate greater perceived stress. The European Spanish adaptation of the PSS-14 has demonstrated acceptable psychometric properties, including good internal consistency (Cronbach’s alpha = .81), satisfactory test-retest reliability (r = .73), and evidence of concurrent validity and sensitivity [20].

#### Quality of Life by PedsQL™ Family Impact Module (PedsQL-FIM).

To assess the impact of paediatric chronic health conditions on caregivers and the family, the Spanish version of the PedsQL™ Family Impact Module will be used [15,21]. This module employs a multidimensional parent self-report to evaluate physical, emotional, social, and cognitive functioning, as well as communication and worry. The module can be completed within 5–10 minutes [21,22] The Pediatric Quality of Life Inventory Family Impact Module (PedsQL-FIM) will be utilized to evaluate the impact of paediatric health conditions on caregiver and family functioning. This instrument consists of 36 items, demonstrating excellent internal consistency reliability (Cronbach’s α = 0.97) (21). It measures eight core dimensions: physical functioning (6 items), emotional functioning (5 items), social functioning (4 items), cognitive functioning (4 items), communication (3 items), worry (5 items), daily activities (3 items), and family relationships (5 items). Responses are rated on a 5-point Likert scale (0 = never a problem to 4 = almost always a problem), then reverse scored and linearly transformed to a 0–100 scale (0 = 100, 1 = 75, 2 = 50, 3 = 25, 4 = 0), with higher scores indicating better perceived functioning. The total score is calculated by summing all item scores and dividing by the number of items completed [23].

#### Zarit Burden Interview (ZBI).

The Zarit Burden Interview is a widely used self-report instrument for measuring caregiver burden. ZBI assesses caregivers´ perceptions of burden that may inadvertently affect their health, personal, social or financial wellbeing [16].

Caregivers are requested to assess the level of burden they experience while caring for a loved one. Burden is defined as the degree to which a caregiver perceives negative effects on their emotional and physical health, social life, and finances, which may hinder their ability to provide care. Responses vary from “not at all” to “extremely.” It consists of 22 items, with the total score calculated by summing the scores of all the indicated items. It is suggested that a score from 0 to 21 means no to mild burden, 21–40 indicates mild to moderate burden, 41–60 indicates moderate to severe burden, and more than 61 means severe burden [24].

The Spanish version developed by Martin-Carrasco et al. [25] showed a good internal reliability (Cronbach alpha coefficient of 0.92) [17,26].

### Data analysis

#### Quantitative data.

The quantitative data will be analysed using descriptive statistics and frequency counts. Sociodemographic characteristics will be described. Descriptive statistics will be reported with means and standard deviations for continuous variables with normal distribution (age, child’s age, PSS-14, PedsQL-FIM, ZBI), or medians and interquartile ranges for variables without normal distribution. For categorical variables (sex, educational level, severity), both absolute and relative frequencies will be presented.

For the inferential analyses, Spearman’s correlations will be used to explore relationships among questionnaires (stress, burden, and quality of life) as well as to correlate caregiver outcomes (stress, burden, quality of life) across subgroups defined by sociodemographic variables (e.g., economic status, education level), child-related variables (e.g., severity of Cerebral Palsy, mobility), and caregiving factors (e.g., relation with the child). Primary analyses will use multivariable linear regression to model each caregiver outcome: (i) perceived stress (PSS-14), (ii) caregiver burden (ZBI), and (iii) quality of life (PedsQL-FIM total). Separate regression models are specified for stress, caregiver burden, and quality of life, consistent with their conceptualization as co-primary constructs, each examined to characterize different but interrelated dimensions of caregiver outcomes. Given the finite population constraints (approximately 40 eligible caregivers)), each model will include only the most relevant predictors (up to 2–3 per model), carefully selected on priori literature and clinical plausibility (e.g., socioeconomic status, caregiving duration, and child functional severity/mobility). This parsimonious approach reduces multiple comparisons and allows adjustment for potential confounders. Model assumptions, including linearity, normality of residuals, and homoscedasticity, will be evaluated using standard diagnostics such as residual plots and Shapiro-Wilk tests. If model assumptions are violated, data transformations or alternative statistical techniques will be considered. Results will be reported as standardized regression coefficients (β) with 95% confidence intervals. Analyses will be conducted using IBM SPSS Statistics v28 (or equivalent software) with significance level of α = 0.05 (two-tailed).

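### Spearman's correlation is the method named for all subgroup factors, including relation with the child, which is unordered; with three or more categories the result depends on how they are numbered

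*Protocol article*

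**What the plan says.** Under Data analysis, Quantitative data, one sentence gives Spearman's correlation two jobs. The first is pairs of scores: "Spearman’s correlations will be used to explore relationships among questionnaires (stress, burden, and quality of life"). The second is "to correlate caregiver outcomes (stress, burden, quality of life) across subgroups defined by sociodemographic variables (e.g., economic status, education level"), then "child-related variables (e.g., severity of Cerebral Palsy, mobility"), then "and caregiving factors (e.g., relation with the child"). No other method for relating an outcome to a group is named, and no coding or list of categories is given.

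The next sentence sets these analyses apart from the main ones: "Primary analyses will use multivariable linear regression to model each caregiver outcome". Each model takes two or three predictors; the examples are socioeconomic status, caregiving duration and child severity or mobility. The only fallback is "If model assumptions are violated, data transformations or alternative statistical techniques will be considered", which follows the regression diagnostics. Tests use a "significance level of α = 0.05 (two-tailed").

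The Inclusion criteria admit any adult caregiver of a child with Cerebral Palsy, without restriction to parents.

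**The concern.** Spearman's rho ranks both variables and measures how far one rises or falls with the other. It needs a variable whose values can at least be put in order. Relation with the child, read as who the caregiver is to the child, cannot. To compute rho, someone must number the categories. With three or more, different numberings are different hypotheses, and the software returns a different coefficient and p-value for each.

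Two analysts following the plan exactly could therefore report opposite signs or opposite significance from the same data. Relation with the child is not among the example regression predictors, so Spearman is the only inferential method the article ties to it. What is at stake is whether that secondary result can be interpreted.

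**Working it through.** **1. The plan's own figures.** They reproduce, and they do not depend on this point.
- Precision, from Sample size considerations (SD 21, ±5 points, 95% confidence, population 40): n0 = (1.96 × 21 / 5)² = 67.76. With the finite-population correction, n = 67.76 / (1 + 66.76/40) = 25.39, rounded up to 26.
- Attrition of 15%: 26 / 0.85 = 30.6, rounded up to 31.
- Correlation power by Fisher's z, Φ(atanh(r)·√(n − 3) − 1.96): 80.9% for n = 25, r = 0.54, and 81.4% for n = 30, r = 0.50.

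**2. Which listed factors are affected.**

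| Factor in the Spearman sentence | Can be ordered? | Spearman defensible? |
|---|---|---|
| Economic status | yes | yes |
| Education level | yes | yes |
| Severity of Cerebral Palsy | yes | yes |
| Mobility | yes | yes |
| Relation with the child | no, on the natural reading | only with two levels |

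**3. Two levels.** Swapping the codes reverses the ranks, so rho changes sign and nothing else. In an invented set of 26 caregivers split 15 against 11, rho was +0.41 or −0.41, with p = 0.037 both times.

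**4. Three levels, simulated.** From the protocol: n = 26 and α = 0.05, two-sided. Assumed, because the protocol gives no such figures: groups A, B and C of 13, 8 and 5; true means 0, +12 and −8; normal errors with within-group SD 17. The second set of results uses 21, the only SD in the protocol; it is a normative SD for the PedsQL-FIM, not a within-group SD.

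| Numbering (low to high) | Mean rho, SD 17 | p < 0.05, SD 17 | p < 0.05, SD 21 |
|---|---|---|---|
| A, B, C | −0.01 | about 3% | about 4% |
| A, C, B | +0.23 | about 20% | about 15% |
| B, A, C | −0.39 | about 52% | about 36% |
| Kruskal-Wallis (no numbering) | – | 38% | 26% |

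The three remaining numberings are these reversed, so only the sign of rho differs. Simulation error is about one or two percentage points.

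**5. A second configuration.** With assumed groups of 10, 8 and 8 and one group shifted by 1 SD, Spearman rejected in about 4% or about 45% of samples depending on the numbering; Kruskal-Wallis rejected in 46%.

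**6. No true difference.** With the 13/8/5 split and equal means, each fixed numbering rejected in about 5% of samples. The false-positive rate therefore holds for a coding fixed in advance.

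**The case against.** The strongest reply is that this is one example factor in a secondary analysis. The regressions are primary, the article describes itself as exploratory, and the hypotheses are sent to the regression models. All of that stands and limits the weight of the point, but it does not make the coefficient interpretable.

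A second reply is that the wording is loose. If correlating across subgroups means correlating the scores with each other within each subgroup, coding does not matter. But 26 completers in two or three groups leave about 13 or 9 per correlation, and no comparison between groups would then be specified. If relation meant a rated quality of relationship, it would be ordinal. Neither is the natural reading, and either would need saying.

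A third reply is that the clause on alternative techniques covers this. It does not: it is triggered by violated regression assumptions.

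A reader might also infer more than the documents support:
- *That Spearman is wrong for the subgroup factors in general.* Four of the five listed examples can be ordered.
- *That type of Cerebral Palsy is affected too.* It appears in hypothesis 3, which is assigned to the regressions. The Spearman sentence names severity and mobility.
- *That the p-values produce excess false positives.* They do not when the coding is fixed beforehand. What suffers is meaning and power. The false-positive rate is at risk only if the numbering is chosen after results are seen.
- *That this correlation decides who is interviewed.* The article says in general terms that quantitative results guide selection, and it ties the interview subgroup to PedsQL-FIM and Zarit categories. Nothing links selection to this coefficient.

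**Conclusion.** The point holds for unordered factors with three or more categories. Of the factors listed, that means relation with the child. The method stated for it gives a coefficient and p-value that depend on arbitrary numbering, so this is a wrong choice as written rather than detail left to a fuller document.

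Two assumptions carry the conclusion: that relation means the caregiver's kinship or role, and that at least three categories are kept. If the factor is reduced to two, only the sign of rho is arbitrary. The dependence on coding is a mathematical property. The simulated rejection rates, roughly 3% to 52% with SD 17 or 4% to 36% with SD 21, illustrate it under invented group sizes and means and are not forecasts for this study.

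The primary regressions, the sample size and the Spearman correlations between scores or with ordinal factors are untouched. This is a should-fix correction to a secondary, exploratory analysis.

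**What to change.** Split the sentence by type of variable. Keep Spearman's correlation for pairs of questionnaire scores and for ordinal factors such as education, economic status, severity and mobility. For nominal factors such as relation with the child, name Mann-Whitney for two groups and Kruskal-Wallis for three or more. Report group medians or mean differences with 95% confidence intervals. List the categories, and settle any pooling of small ones, before outcome data are seen. If within-subgroup correlations were intended, say so and state how groups will be compared.

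The cost is about one sentence of analysis wording. No new data, sample-size change or additional software is needed.
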